## Sample size determination

Assuming the historical rate of pCR with short radiation followed by systemic 5FU-oxaliplatin chemotherapy is 16% to 19% (Bujko et al., 2016a) and the rate of pCR with the addition of avelumab increases to 35%, Simon’s two-stage design (Simon R, 1989) will be used. The null hypothesis that the true response rate is ≤16% will be tested against a one-sided alternative. In the first stage, 13 patients eligible for the primary efficacy analysis will be accrued. If there are 2 or fewer patients with a pCR in these 13 patients (2 patients out of 13 constitutes 15%), the study will be stopped. Otherwise, 23 additional (eligible) patients will be accrued for a total of 36 patients eligible for the primary efficacy analysis. The null hypothesis will be rejected if at least 10 patients out of 36 have a pCR. This design yields a type 1 error rate of 0.05 and a power of 0.8 when the true pCR rate is 35%. The use of the Simon 2-stage design enables an interim analysis for both efficacy and safety to be performed following treatment of the first 13 (eligible) patients. In order to achieve the eligible 36 patients for the primary efficacy analysis, the study might have to recruit 15 to 20% more patients and this will increase the sample size to 44 patients. This increase in sample size will also benefit the analysis of the secondary outcomes for example by possibly increasing the precision with the estimation of the progression free survival outcome.

## Randomization

Not applicable.

## Protocol deviations and analysis sets

All the deviations from protocol definitions will be listed and defined as major or minor deviations in the SAP.

According to the proposed analysis, the definition of analysis sets is recommended as follows:

- - 1. ITT set: all patients who received at least one administration of the IMP.
    2. Modified ITT Set (MITT): all ITT patients who received at least one administration of IMP, with (the baseline) assessment available and have undergone surgical resection. When further restrictions/qualifications are suggested, they must be specified in a protocol amendment.
    3. Full-Analysis Set (FAS): all patients who received at least one administration of IMP.
    4. Total Treated Set: all patients who received at least one administration of IMP.
    5. Per Protocol (PP) Set: all MITT patients without major deviations. These major deviations must be defined in the protocol or in the SAP.

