## Discontinuation criteria / stopping rule(s)

The Investigator must document the reason of any patient withdrawal or discontinuation by a narrative description.

A patient may be discontinued from the study at any time for one or more of the following reasons:

1. Occurrence of an AE that, to the judgment of the Investigator or the Principal Investigator, may interfere with study conduct or study results
2. Protocol deviation that could invalidate the interpretation of the results
3. Lack of efficacy if relevant, to be defined on a “case by case” basis
4. Withdrawal of consent for any reason, at any time
5. Lost to follow-up
6. Administrative problems
7. Investigator decision in patient best interest
8. Pregnancy
9. Death

Data to be collected are detailed in Section 8.

The study can be stopped depending on the results of the interim analysis in this 2-stage study.

If a patient withdraws from the study or if the treatment is discontinued, the Investigator will make every effort to complete the final evaluation by performing an "end of study visit". All evaluation results, the date and a narrative description of the reason(s) for discontinuation must be recorded in the source documents and in the electronic Case Report Form (eCRF).

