## General rules for handling of missing or inconsistent data

No replacement of missing data will be performed except for:

- - 1. The primary efficacy endpoint is a dichotomous criterion (yes/no). A missing primary endpoint will be considered as if the endpoint is not fulfilled (no pCR).
    2. The duration would be based on the time difference between the date the patient signs the informed consent and is enrolled in the study and the date of progression of disease on imaging. Otherwise, if the patient’s disease did not progress, the patient will be censored in the analysis and the last follow-up date or date of last communication with the patient will be applied instead.

All estimated or replaced data will be edited along with a flag in the statistical appendices.

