## Demographic and baseline characteristics

Demographic and baseline characteristics of all patients in the FAS will be analyzed.

The primary efficacy analysis will be performed on the MITT set.

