## Efficacy analysis

### Primary efficacy variable(s)

- - 1. ***Description of the primary efficacy variable***

The primary endpoint is the proportion of patients who achieve a pathologic complete response, defined as no viable tumor cells on the resected specimen, in the MITT set.

The primary efficacy variable is a dichotomous variable (yes/no) that will be summarized using a proportion.

- - - 1. ***Hypothesis Test and Primary Analysis Model***

A Simon’s two-stage optimal design will be applied with the following hypothesis:

- H0: p (pCR) ≤0.16
- H1: p (pCR) ≥0.35

If 2 or less patients achieved pCR in the first stage with 13 MITT patients, the study will be stopped, otherwise another 23 MITT patients will be added to the study (stage 2) and the results of the 36 MITT patients will be analyzed at the end of the study. If overall 10 or more patients achieved pCR, then the null hypothesis will be rejected with a type I error of 0.05.

In addition, the one-sided 95% confidence interval (Wilson Score method) of the percentage of patients with pCR will be estimated for all patients in the MITT set and the PP set.

- - - 1. ***Multiple comparisons and interim analyses***

Interim analysis will be done upon recruitment of the first 13 MITT patients to assess the futility and efficacy of the study.

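### The primary pCR rate is tested and estimated only in resected patients, so the rate per treated patient, which the objective asks for, is never estimated

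*Protocol*

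**What the plan says.** The primary objective (Section 2.1) is the pCR rate following short-course radiation and then mFOLFOX-6 with avelumab. pCR is defined on the resected specimen (Section 3.2).

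Section 12.4 defines the ITT, FAS and Total Treated sets identically, as everyone given at least one dose of avelumab. The MITT set is narrower: "all ITT patients who received at least one administration of IMP, with (the baseline) assessment available and have undergone surgical resection". PP is MITT without major deviations.

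Section 12.6 states: "The primary efficacy analysis will be performed on the MITT set". In Section 12.8.1 both Simon stages (13, then 36) count MITT patients, and the Wilson limit "will be estimated for all patients in the MITT set and the PP set". No pCR analysis uses ITT, FAS or Total Treated, whereas Section 12.8.2 analyses PFS in ITT, MITT and PP.

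On missing data, Section 12.5 says: "A missing primary endpoint will be considered as if the endpoint is not fulfilled (no pCR".

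On the design, Section 12.2 says: "The null hypothesis that the true response rate is ≤16% will be tested against a one-sided alternative". It assumes that "the rate of pCR with the addition of avelumab increases to 35"%. The synopsis expects 15 to 20% of patients not to be eligible for the primary analysis, which takes 36 up to 44 enrolled.

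**The concern.** Membership of the primary set depends on an event after treatment starts, namely surgery. A treated patient who progresses, dies, becomes unfit or declines the operation cannot be a pCR, because there is no specimen. Such a patient is a failure of the strategy named in the objective, but is dropped instead of being counted as one.

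The missing-data rule might be expected to cover this case. In the primary analysis it can act only within MITT, on a resected patient without a pathology result. The patient with no resection has already been removed by the set definition.

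At stake is how a positive result is read. Success on the MITT test is a statement about patients who reached surgery. The protocol plans no estimate that would show whether the same holds per treated patient.

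**Working it through.** **Inputs.** Null rate 0.16, alternative 0.35, stop at 2 or fewer of 13, reject at 10 or more of 36 (Section 12.2). Early-termination probability 65.37% (Section 4). Share not eligible for the primary analysis 15 to 20% (synopsis). The share of treated patients who are never resected, d, is not given, so it is varied from 0 to 20%.

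**1. The plan's own figures.** With X1 ~ Bin(13, p) and X2 ~ Bin(23, p),

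P(reject) = sum over x = 3 to 13 of P(X1 = x) × P(X2 ≥ max(0, 10 − x)).

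- p = 0.16: P(reject) = 0.0433; P(X1 ≤ 2) = 0.6537, as stated.
- p = 0.35: P(reject) = 0.8008.

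This agrees with the statement that "This design yields a type 1 error rate of 0.05 and a power of 0.8 when the true pCR rate is 35"%, taking 0.05 as a ceiling. The design is correct for an MITT denominator.

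**2. Direction.** No unresected patient can be a pCR. So, for the resection condition, MITT rate = treated rate / (1 − d), which is never below the treated rate.

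**3. Size on the test.** Set the treated rate at 16% and apply the same rule at 0.16 / (1 − d):

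| d | MITT rate | P(reject) |
|---|---|---|
| 0% | 16.0% | 4.3% |
| 5% | 0.16/0.95 = 16.8% | 5.8% |
| 10% | 0.16/0.90 = 17.8% | 7.8% |
| 15% | 0.16/0.85 = 18.8% | 10.6% |
| 20% | 0.16/0.80 = 20.0% | 14.3% |

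**4. Size on the estimate.** The one-sided 95% Wilson lower limit, with z = 1.645 and p̂ = x/n, is

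[p̂ + z²/(2n) − z√(p̂(1 − p̂)/n + z²/(4n²))] / (1 + z²/n).

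At the minimum success count of 10:

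- 10/36 = 27.8%: (0.3154 − 0.1284)/1.0752 = 17.4%, above 16%.
- 10/38 = 26.3% (two unresected): 16.4%, still above 16%.
- 10/39 = 25.6% (three unresected): (0.2911 − 0.1201)/1.0694 = 15.99%, just below 16%.

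**5. Cost of moving the formal test.** If 35% was meant per resected patient and unresected patients count as failures, the treated rate is 0.35 × 0.85 = 29.8% at d = 15% and 0.35 × 0.80 = 28.0% at d = 20%. Power of the unchanged 10/36 rule is then 0.60 and 0.51.

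**The case against.** The strongest reply is that the design may already compare like with like. Section 12.2 does not say whether the historical 16 to 19% is per treated or per resected patient. If it is per resected patient, the MITT test has its designed error of 4.3%. Testing all treated patients against 16% would then be the mismatch: at 15 to 20% unresected the null rate becomes 13.6 to 12.8%, and rejection falls to 1.6 to 1.1%. This stands. It limits the claim about the test, but not the absence of an estimate per treated patient.

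Four stronger readings are tempting, and the documents do not support them.

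- A reader might take the 44 as treated patients and compare 10/36 with 10/44 (lower limit 14.1%). But 44 are enrolled, and enrolment is signature of consent (Section 8.1.2). The eight extra also cover patients who never receive avelumab, first given at D15, and those without a baseline assessment. For the same reason, 15 to 20% is a ceiling for d and not an estimate of it.
- A reader might infer that toxicity alone removes patients. MITT needs one dose plus resection, so a patient who stops avelumab and is then operated on stays in. Section 17 also provides for abdominoperineal resection where TME is not possible.
- A reader might see Section 5.4 as a way to delete failures. It lists "Lack of efficacy if relevant, to be defined on a" case-by-case basis as a possible reason for discontinuation, but nothing there cancels surgery.
- A reader might call Sections 12.4 and 12.5 contradictory. Section 12.5 is a general rule that names no analysis set and still has a use within MITT.

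It can also be said that a supportive all-treated table is SAP material. That is partly fair. However, the protocol itself fixes the primary set, the missing-data rule and the sets in which pCR is estimated, and it names ITT for PFS but not for pCR.

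**Conclusion.** The point holds. The protocol restricts the pCR test and its confidence limit to resected patients and plans no estimate per treated patient, although the objective concerns the regimen and an ITT set is already defined. The direction of the resection condition is certain: it can only leave the rate unchanged or raise it.

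The size is a range. With a true rate of 16% per treated patient, the chance of declaring success runs from 4.3% with everyone resected to 14.3% with 20% unresected. The 10.6% and 14.3% figures assume that the whole 15 to 20% are treated but unresected. Every figure above 4.3% assumes that the historical 16% is per treated patient. At the minimum success count, three treated but unresected patients are enough to bring the lower limit below 16%.

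The documents do not show that the test's type I error is in fact inflated, because the historical denominator is not given.

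**What to change.** In Section 12.8.1, pre-specify the pCR proportion with its one-sided 95% Wilson limit in the ITT set of Section 12.4, counting every patient without a resection as no pCR. Require it to be quoted beside any success claim based on the MITT test. In Section 12.2, state whether the 16% and the 35% are per treated or per resected patient.

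The cost is a short amendment and one extra table. The reported rate will be less favourable if any treated patient is unresected. Stage sizes, boundaries and the formal test do not change.

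Moving the formal test to all treated patients is optional and is a real trade-off. It changes who counts in both stages and would need the null rate, the alternative and the sample size to be re-derived on that denominator. With the present 10/36 rule, power would be about 0.60 to 0.51 at 15 to 20% unresected if 35% was meant per resected patient.

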## General rules for handling of missing or inconsistent data

No replacement of missing data will be performed except for:

- - 1. The primary efficacy endpoint is a dichotomous criterion (yes/no). A missing primary endpoint will be considered as if the endpoint is not fulfilled (no pCR).
    2. The duration would be based on the time difference between the date the patient signs the informed consent and is enrolled in the study and the date of progression of disease on imaging. Otherwise, if the patient’s disease did not progress, the patient will be censored in the analysis and the last follow-up date or date of last communication with the patient will be applied instead.

All estimated or replaced data will be edited along with a flag in the statistical appendices.

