#### *Analysis of secondary efficacy variables*

Mainly, PFS will be estimated using Kaplan Meier methods. Median PFS and the PFS rate at 3 years and corresponding 95% confidence intervals will be presented. PFS will be defined for all patients regardless of their pCR as the time between the date the patient is enrolled in the study and the date the disease progression is shown on imaging or the date of death whatever is earlier and the last follow up date in the absence of disease progression or death. Patients without progression or death will be censored at the last assessment regarding progression. PFS will be analyzed for the ITT, the MITT and the PP set.

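### Protocol Section 12.5 ends progression time only at imaging progression and so, read literally, censors deaths, whereas Section 12.8.2 counts death as a PFS event and itself gives two censoring dates

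*Protocol*

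**What the plan says.** Section 12.5 (missing or inconsistent data), item 2, describes a duration without naming it. It starts at "the date the patient signs the informed consent and is enrolled in the study" and ends at imaging progression: "and the date of progression of disease on imaging". For a patient whose disease did not progress, the rule is "the patient will be censored in the analysis and the last follow-up date or date of last communication with the patient", used in place of a progression date.

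Section 12.8.2 (analysis of secondary efficacy variables) defines PFS by name. Its starting point is given by "the time between the date the patient is enrolled in the study". Its end point, unlike that of Section 12.5, includes death: "the date the disease progression is shown on imaging or the date of death whatever is earlier". The same sentence goes on to give "the last follow up date in the absence of disease progression or death" as the end date for patients with neither event. The next sentence gives another date: "Patients without progression or death will be censored at the last assessment regarding progression".

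The start dates agree, because Section 8.1.2 treats a patient as enrolled once consent is signed. Being progression free at 3 years is the first secondary objective (Section 2.2).

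**The concern.** The two sections can treat the same patient differently. Someone who dies after surgery, or from toxicity, with no progression on a scan is an event under Section 12.8.2. Under the literal rule of Section 12.5 that patient did not progress and is therefore censored. The protocol itself recognises that such deaths can occur: Section 9.2.1 lists fatal immune-related reactions seen with avelumab, and the surgical complication scale in Section 9.2.2 includes death.

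The trial has one arm, and Section 9.2.3 names a higher 3-year PFS rate than historical controls as an expected benefit. A lenient event rule would not cancel between groups. It would feed straight into that comparison, always in the favourable direction.

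The protocol does not leave this open for the SAP. It fixes the rule twice, differently, so whichever version the SAP adopts departs from one section. Section 12.1 requires departures from the protocol's statistical description to be discussed in the study report.

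**Working it through.** The protocol states no PFS event count, power or sample size, so there is no PFS figure to reproduce. The check compares the rules and then sizes the consequence.

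**Rules side by side**

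| Element | Section 12.5, item 2 | Section 12.8.2 |
| --- | --- | --- |
| Start | Consent/enrolment | Enrolment (the same date) |
| Event | Imaging progression | Imaging progression or death, whichever is first |
| Death without progression | Not mentioned; censored on a literal reading | Event |
| Censoring date | Last follow-up or last contact | Last follow-up, then, in the next sentence, last progression assessment |

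**Event conflict, early deaths**

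Inputs: 44 planned patients (Section 5.1); a 3-year rate of about 50% (Section 1.1, historical disease-free survival, used only as an illustration); d early deaths without progression (assumed: 2, 3 or 4).

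If the d deaths precede all other events and censorings, counting them multiplies the Kaplan-Meier estimate by (1 − d/44). Censoring them removes that factor and leaves the later risk sets unchanged. The estimate under Section 12.5 is therefore 0.50/(1 − d/44):

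- d = 2: 0.50/(42/44) = 52.4%
- d = 3: 0.50/(41/44) = 53.7%
- d = 4: 0.50/(40/44) = 55.0%

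**Event conflict, deaths spread over follow-up**

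With constant hazards, let s be the share of PFS events that are deaths without imaging progression (assumed; the protocol gives none). If 3-year PFS is S with deaths counted, censoring them gives S^(1−s), and the median lengthens by 1/(1−s).

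| s | From S = 50% | From S = 70% | Median multiplied by |
| --- | --- | --- | --- |
| 5% | 51.8% | 71.3% | 1.05 |
| 10% | 53.6% | 72.5% | 1.11 |
| 20% | 57.4% | 75.2% | 1.25 |
| 30% | 61.6% | 77.9% | 1.43 |

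**Censoring-date conflict**

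A Kaplan-Meier simulation used 44 patients, 3-monthly assessments, a true 3-year PFS of 50%, assumed loss to follow-up of 10% or 20% by 3 years, and 800 runs per setting. Deaths were counted, and only the censoring date was switched between last contact and last 3-monthly assessment. The mean 3-year estimate changed by 0.1 point or less in every setting (for example 49.9% against 50.0% at s = 10% and 10% loss). In this set-up, last contact is never more than one 3-month interval after the last assessment. Longer gaps were not simulated.

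**The case against.** The strongest reply is that Section 12.5 is a general missing-data rule, not a rival endpoint definition. It names neither PFS nor death, and a recorded death date is not missing data. Section 12.8.2 is the specific definition, it expressly counts death, and a specific definition normally governs. A reader might infer that the protocol deliberately censors deaths. The text does not support that: the censoring follows from silence. The conflict nevertheless stands. Time from consent to imaging progression, with censoring, can only be PFS in this trial, and an analyst who follows item 2 as written would censor those deaths.

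A reader might also infer that both conflicts inflate PFS materially. The documents do not support that for the censoring date. Disease status is scheduled at every 3-monthly visit and at the end of study (Table 1, Sections 8.2.6 and 8.2.7), so last follow-up and last assessment should usually be close. The date would matter more if only imaging counted. Table 1 schedules CT or PET only at inclusion, and Section 17 lists follow-up imaging as standard of care without a timetable.

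The sizing is also open to fair criticism. The death counts are assumed and the 50% is not a PFS rate. PFS is analysed in the ITT, MITT and PP sets rather than in all 44 enrolled. ITT requires a dose of avelumab and MITT requires surgery, so some early deaths leave those sets under either rule. Sampling error is larger than the shift: at 50% with 44 patients and no censoring, the 95% half-width is about 1.96 × √(0.25/44) = 15 points. All of this limits the severity. None of it makes the two rules agree, and a one-directional bias is not excused by a wide interval.

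**Conclusion.** The inconsistency is real and in the current text. Its material part is the event: Section 12.5, applied literally, drops deaths without imaging progression and raises 3-year PFS. The rise is roughly 2 to 5 points from an illustrative 50% if 2 to 4 of about 44 patients die early without progression. If such deaths made up 20% to 30% of all PFS events it would be about 7 to 12 points. Both ranges rest on assumed deaths and a historical disease-free survival rate.

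The two censoring dates inside Section 12.8.2 are a drafting fault of small effect, provided that the 3-monthly disease-status visits count as progression assessments.

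It would be wrong to conclude that the trial's main result is at risk. The stage 1 stopping rule and the final test use pCR only, and PFS carries no hypothesis, threshold or alpha. Severity is moderate.

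**What to change.** 1. Keep Section 12.8.2 as the only PFS definition: time from enrolment to the first of progression shown on imaging or death from any cause.
2. Replace item 2 of Section 12.5 with a cross-reference to Section 12.8.2.
3. In Section 12.8.2, delete the whole clause "the last follow up date in the absence of disease progression or death", together with the conjunction that introduces it. The defining sentence then ends at the earlier of the two events, and the only censoring rule is the following sentence, which uses the last progression assessment. Deleting only part of the clause would leave a sentence without meaning.
4. State that the scheduled 3-monthly disease-status assessments count as progression assessments for censoring. Without this, an event-free patient with no scan after inclusion could be censored near baseline, because no follow-up imaging is scheduled.

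The event stays imaging-based as now written; nothing here argues for widening it. The cost is a short edit to two sections, carried into the SAP, with no new data or visits. It should be made before PFS results are seen, so that the choice cannot depend on them. The downside is that the reported PFS may be slightly lower than under Section 12.5.
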